- **Group 2:** Receiving conventional sepsis therapy in addition to fluoxetine 40 mg ( Prozac 20mg , Elli Lillys medical company Indianapolis, Indiana, United States) ® (1) daily for 28 days or until discharge from the ICU or death.
- **Primary outcome:** vasopressor dose.
- **Secondary outcome:** ICU Mortality & Organ dysfunction.

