### **Clinical Data:**

- To be evaluated up to a maximum follow-up period of 28 days of ICU stay:
  - Length of hospital stay
  - Need for and duration of mechanical ventilation
  - Need for and duration of vasopressor and inotropic support
  - Need for hemodialysis
  - Final outcome:
    - Survivors:
      - A) Patients recovered and discharged from ICU.
      - B) Patients still morbid and stayed in ICU more than 28 days.
    - Non-survivors:
      - Death before the completion of the 28 days of study period.

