### **Application of APACHE II and SOFA Scoring Systems:**

- APACHE II score to be evaluated on study day 1.

- SOFA score to be evaluated on study day 1 and serially every day until ICU discharge or death or up to 28 days.

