### Statistical Analysis and Sample Size:

- Data entry, processing, and statistical analysis will be carried out using SPSS v29. Frequency tables with percentages will be used for categorical variables and descriptive statistics (mean  $\pm$  standard deviation or median with interquartile range) will be used for numerical variables. Tests of significance (Chi-square, student's t-test, or Mann Whitney's test) will be used according to the normality of the data. A P-value of less than 0.05 will be considered statistically significant. Total sample size 52 cases (organ dysfunction using SOFA score will be used as a primary outcome with proposed large effect size (0.8) and  $\alpha=0.05$  and power=0.80, so, 26 cases are needed in each group).

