### Statistical Analysis:

- Results will be expressed as mean  $\pm$  standard deviation or number (%). Comparison between categorical data will be performed using the Chi-square test. Comparison between different numerical data in the two studied groups will be performed using an unpaired t-test. Comparison between different times of measurements and baseline within the same group will be performed using repeated measure ANOVA. The SPSS computer program will be used for data analysis. P value less than 0.05 will be considered significant.

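### The trial is sized on SOFA as a single-test outcome, but SOFA is scored daily for up to 28 days and no day or summary is named to decide the result

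*Protocol*

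**What the plan says.** The protocol's Statistical Analysis and Sample Size section states "organ dysfunction using SOFA score will be used as a primary outcome with proposed large effect size (0.8", with alpha 0.05, power 0.80 and 26 cases per group (52 in total). It does not say whether the 0.8 refers to SOFA on a given day, a change, a maximum or a mean.

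The section on APACHE II and SOFA sets the schedule: "SOFA score to be evaluated on study day 1 and serially every day until ICU discharge or death or up to 28 days". A patient who stays in the ICU throughout has a day-1 value and up to 27 later ones.

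The final Statistical Analysis section gives the between-group rule, "Comparison between different numerical data in the two studied groups will be performed using an unpaired t-test", and the threshold, "P value less than 0.05 will be considered significant". The earlier analysis section also allows the Mann-Whitney test, according to normality. Repeated measurement has one further provision: "Comparison between different times of measurements and baseline within the same group will be performed using repeated measure ANOVA".

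The outcome list after the group descriptions reads "Primary outcome: vasopressor dose" and places organ dysfunction among the secondary outcomes. The only vasopressor item under Clinical Data is "Need for and duration of vasopressor and inotropic support".

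**The concern.** A sample size with one effect size, one alpha and one power describes one comparison. SOFA as scheduled supplies up to 27 post-baseline comparisons, before counting summaries such as maximum, mean or change. The stated tests and threshold fit every one of them equally well. The repeated-measures ANOVA does not bring them together, because it compares time points within each group and not the groups with each other.

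Different days of one series can lead to different conclusions. Late days are a particular problem: scoring stops at discharge or death, so those comparisons cover only patients still in the ICU. If the day or summary is chosen after the data are seen, the main result no longer carries a 5% error rate. The effect size of 0.8 also has no fixed meaning, since the same difference in SOFA points gives a different standardised effect on a single day than on a mean over several days.

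**Working it through.** **1. The plan's own figure.** Inputs from the SOFA calculation: d = 0.8, alpha = 0.05, power = 0.80. Sidedness is not stated there, so two-sided is assumed.

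- Normal approximation: n = 2(1.960 + 0.842)²/0.8² = 24.5, so 25 per group.
- Noncentral t: n = 25.5, so 26 per group, with power 80.7% at 26.

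The stated 26 is reproduced as the size for a single two-sample t-test.

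**2. Number of candidate contrasts.** Day 1 is baseline. Days 2-28 give 28 − 1 = 27 daily between-group contrasts, and days 2-7 give 6.

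**3. Upper reference if the days were independent.** 1 − 0.95⁶ = 26.5% and 1 − 0.95²⁷ = 75.0%. Daily scores on the same patient are correlated, so the real rates are lower.

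**4. Simulation under no effect.** Normal data, 26 per group, an unpaired two-sided t-test at 0.05 on each day, 20,000 trials per setting. The documents give no within-patient correlation, so these are assumptions shown as a range. Entries are the probability of at least one P<0.05.

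| Assumed correlation | Days 2-7 (6 tests) | Days 2-28 (27 tests) |
|---|---|---|
| Exchangeable 0.5 | 21.0% | 49.4% |
| Exchangeable 0.7 | 16.4% | 33.3% |
| Exchangeable 0.9 | 10.8% | 17.3% |
| AR(1) 0.80 | 17.3% | 52.4% |
| AR(1) 0.90 | 13.4% | 38.6% |
| AR(1) 0.95 | 10.9% | 27.3% |

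With a single test the same code gives 4.8% to 5.3%, as it should. A separate run of 2,000 trials per setting put the 27-test range at 16.4% to 54.6%. Allowing for both runs, the ranges are about 11% to 21% over days 2-7 and 16% to 55% over days 2-28, or roughly 2 to 4 times and 3 to 11 times the nominal 5%.

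**5. Exit from the ICU.** The settings above keep every patient to day 28. With an assumed 8% leaving per day, equally in both arms, and a day tested only if each arm has at least 5 patients, the 27-day range is 25% to 49% (2,000 trials per setting). Exit changes the figure but does not remove the problem.

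**6. Vasopressor dose.** No dose schedule, unit or summary is given, so there is no defined set of contrasts to simulate, and no figure is offered.

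**The case against.** The strongest reply is that the protocol nowhere prescribes daily between-group tests and nowhere says that one significant day decides the trial. The test and threshold are generic, and the choice of summary and handling of multiplicity are often left to a SAP, which is not shown here. The first part stands: the inflation is conditional on a choice among days, and the percentages are not a property of the plan as such. The second part carries less weight. This protocol has its own analysis sections, fixes the tests and threshold for numerical data, and commits to a size and power for SOFA. Which SOFA value that power belongs to is part of the claim the protocol itself makes.

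A reader might infer that the same inflation applies to whichever outcome is kept. The documents do not support that. Only SOFA is scheduled daily. Clinical Data records need for and duration of vasopressor support, not dose, and the shock duration used in the second sample-size calculation is one number per patient. For vasopressor dose the fault is an undefined endpoint, with no calculable error rate.

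A reader might also infer that the main result certainly loses its 5% error rate. That does not follow either: a single contrast fixed before the data are seen would keep it. The size also depends heavily on correlation; at exchangeable 0.9 the 27-day figure is 16% to 17%, well below the 49% to 55% at the other end.

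**Conclusion.** The point holds for SOFA. The stated 5% and 80% are correct for one contrast (26 per group, 80.7% power at d = 0.8), and the protocol does not name that contrast. If any post-baseline day may decide, the chance of a false-positive finding is about 11% to 21% over days 2-7 and 16% to 55% over days 2-28. These figures rest on assumed correlations (AR(1) 0.80 to 0.95, exchangeable 0.5 to 0.9), normal data and, in the main table, no exit from the ICU.

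For vasopressor dose the conclusion is narrower: unit, window and summary are missing, and no dose record is planned.

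The disagreement over which outcome is primary is a separate matter. Settling it in favour of SOFA or vasopressor dose would still leave the deciding contrast open.

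**What to change.** First reconcile which outcome is primary. Then name one between-group contrast and state that P<0.05 applies to it alone.

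- **If SOFA is kept:** use one summary over one early fixed window, for example mean daily SOFA over study days 2-7, compared between groups with adjustment for day-1 SOFA. State how deaths and ICU discharges inside the window are scored, because scoring otherwise simply stops. State that the effect size of 0.8 refers to this summary.
- **If vasopressor dose is kept:** use one summary over a fixed window in one common unit, add dose recording to the Clinical Data section, and state a rule so that early death does not count as a low dose.
- **In either case:** show any daily curves with 95% confidence intervals and no daily significance tests.

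For SOFA the cost is a few sentences; daily scores and the day-1 value are already scheduled and no patients are added. A dose endpoint costs more, since dose data must be collected. Under both options, effects on other days become descriptive.

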### Statistical Analysis and Sample Size:

- Data entry, processing, and statistical analysis will be carried out using SPSS v29. Frequency tables with percentages will be used for categorical variables and descriptive statistics (mean  $\pm$  standard deviation or median with interquartile range) will be used for numerical variables. Tests of significance (Chi-square, student's t-test, or Mann Whitney's test) will be used according to the normality of the data. A P-value of less than 0.05 will be considered statistically significant. Total sample size 52 cases (organ dysfunction using SOFA score will be used as a primary outcome with proposed large effect size (0.8) and  $\alpha=0.05$  and power=0.80, so, 26 cases are needed in each group).

### Sample Size Calculation:

- The sample size was based on a meta-analysis by Rygård et al. (9), which reported a mean reduction in shock duration of  $-1.52$  days with corticosteroids compared to placebo (95% confidence interval:  $-1.71$  to  $-1.32$ ). Using this effect size, a two-sided alpha of 0.05, and 80% power, we calculated that 23 patients per group (46 total) would be sufficient to detect a statistically significant difference.

Reference: **Rygård SL, Butler E, Granholm A, Møller MH, Cohen J, Finfer S, Perner A, Myburgh J, Venkatesh B, Delaney A.** Low-dose corticosteroids for adult patients with septic shock: a systematic review with meta-analysis and trial sequential analysis. *Intensive Care Med.* 2018 Jul;44(7):1003-1016. doi: 10.1007/s00134-018-5197-6. Epub 2018 May 14. PMID: 29761216.

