## 2. AIM OF THE STUDY:

The aim of this study is to evaluate the efficiency of fluoxetine as an adjuvant therapy in the treatment of severe sepsis and its effect on multiple organ dysfunction and mortality in septic patients.

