## Patients and Methods:

### Study Population:

- ASA II, III 60 patients, aged 18-65 years, BMI 30-35, admitted to ICU and diagnosed as patients with severe sepsis.
- The diagnosis of severe sepsis was established according to the definitions of the Surviving Sepsis Campaign (SSC) (**Singer et al., 2016**).

**Severe sepsis definition = sepsis-induced tissue hypoperfusion or organ dysfunction (any of the following thought to be due to the infection)**

Sepsis-induced hypotension

Lactate above upper limits laboratory normal

Urine output  $< 0.5 \text{ mL/kg/hr}$  for more than 2 hrs despite adequate fluid resuscitation

Acute lung injury with  $\text{Pao}_2/\text{Fio}_2 < 250$  in the absence of pneumonia as infection source

Acute lung injury with  $\text{Pao}_2/\text{Fio}_2 < 200$  in the presence of pneumonia as infection source

Creatinine  $> 2.0 \text{ mg/dL}$  ( $176.8 \text{ }\mu\text{mol/L}$ )

Bilirubin  $> 2 \text{ mg/dL}$  ( $34.2 \text{ }\mu\text{mol/L}$ )

Platelet count  $< 100,000 \text{ }\mu\text{L}$

Coagulopathy (international normalized ratio  $> 1.5$ )

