## Exclusion Criteria:

- Patients with Late septic shock at presentation with multiple organ failure
- APACHE II score on admission >25
- Preexisting liver cirrhosis
- patients with prolonged QT interval or premature ventricular beats
- Preexisting end-stage renal disease
- Pregnancy
- History of allergy to fluoxetine
- Patients with malignancies
- Uncontrolled hemorrhage
- Burns
- Previous steroid therapy
- Death within 24 hours of ICU admission
- Concurrent use of MAO inhibitors or linezolid or any drugs increase QR interval like flecainide
- History of seizures
- Age more than 65 years

Patients will be recruited after admission to the Ain Shams University Hospital. Randomization will be performed using computer-generated random number tables in opaque sealed envelopes prepared by an anesthesiologist who will not participate in the study. Patients will be randomly divided into two groups using a computer-generated random number chart:

- **Group 1:** Receiving conventional sepsis therapy alone according to our hospital protocol (summarized as the following): -
- Initial Resuscitation:

- Patients with sepsis-induced tissue hypoperfusion with suspicion of hypovolemia to achieve a minimum of 30 mL/kg of crystalloids.
- The goals of initial resuscitation of sepsis-induced hypoperfusion included all of the following:
  - MAP  $\geq$  65 mm Hg.
  - Urine output  $\geq$  0.5 ml/kg/hr.
  - CVP 8–12 mm Hg.
  - Central venous oxygen saturation (ScvO2) 70%.
- Diagnosis
- Cultures including blood cultures before antimicrobial therapy if no delay in the start of antimicrobial.
- Antimicrobial therapy
- Iv broad spectrum (one or more anti-infective drug) to cover all likely pathogen according to site of infection and hospital antibiogram.
- Source control
- Source of sepsis should be identified, and intervention should be taken as soon as possible to control it (e.g. surgical drainage and change of infected lines)
- Vasopressor
- If adequate fluid resuscitation therapy was not able to restore hemodynamic, Vasopressor therapy initiated to target a mean arterial pressure (MAP) of 65 mm Hg.
- Norepinephrine as the first-choice vasopressor, epinephrine added to and potentially substituted for norepinephrine when an additional agent is needed to maintain adequate blood pressure
- Corticosteroids
- If adequate fluid resuscitation and vasopressor therapy are not able to restore hemodynamic stability, IV hydrocortisone at a dose of 200 mg/day.

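### The 23-per-group calculation uses an effect measured in septic shock, but the trial enrols severe sepsis without requiring shock, so its 80% power holds only if essentially every patient has shock

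*Protocol*

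**What the plan says.** The Sample Size Calculation cites a meta-analysis that "reported a mean reduction in shock duration of" 1.52 "days with corticosteroids compared to placebo", with a 95% confidence interval of 1.32 to 1.71 days. The reference printed below it is titled "Low-dose corticosteroids for adult patients with septic shock: a systematic review with meta-analysis and trial sequential analysis". The protocol concludes: "Using this effect size, a two-sided alpha of 0.05, and 80% power, we calculated that 23 patients per group (46 total") would be enough. It gives no SD, no expected share of patients in shock, and no adjustment for population.

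The Aim is to "evaluate the efficiency of fluoxetine as an adjuvant therapy in the treatment of severe sepsis". Study Population plans "ASA II, III 60 patients, aged 18-65 years, BMI 30-35, admitted to ICU and diagnosed as patients with severe sepsis" and defines the condition as "sepsis-induced tissue hypoperfusion or organ dysfunction (any of the following thought to be due to the infection"). Nine criteria follow. One is hypotension. The others are raised lactate, low urine output, two lung-injury thresholds, creatinine, bilirubin, platelets and INR.

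The Exclusion Criteria remove "Patients with Late septic shock at presentation with multiple organ failure". Under the conventional therapy described for Group 1, a vasopressor is started only when fluids have not restored haemodynamics. Clinical Data records whether vasopressor support was needed as well as how long it lasted.

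**The concern.** Every patient behind the 1.52-day figure belonged to a septic-shock population and had shock time that could be shortened. In this trial a patient can qualify on creatinine or platelets alone, never need a vasopressor, and contribute zero shock days whichever group he or she is in. Such patients pull the mean difference over all randomised patients below 1.52 days. The mix of zeros and positive durations also changes the SD.

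This is a separate matter from the effect belonging to another drug and from the missing SD. It would remain if fluoxetine matched the corticosteroid effect exactly and the SD among shock patients were known. At stake is the statement that 23 per group is enough, which a reader will take to apply to the population enrolled.

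**Working it through.** **Inputs from the protocol.** Difference 1.52 days, two-sided alpha 0.05, power 80%, 23 per group (Sample Size Calculation); unpaired t-test (Statistical Analysis); 60 patients (Study Population), taken here as 30 per group.

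**Assumptions, none stated in the protocol.** S is the SD of shock duration among patients with shock. p is the share of patients who have shock, the same in both arms. m is the mean control shock duration among those patients.

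**Step 1: the plan's own figure.** Without an SD, 23 per group cannot be reproduced. Solving backwards with the noncentral t, 23 per group at 80% power needs a standardised difference of 0.845, so S = 1.52 / 0.845 = 1.80 days. (The normal approximation gives 1.84.) Reading 1.52 itself as a standardised effect would need only 7 to 8 per group, so that is not what was done.

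**Step 2: add patients without shock.** Let μ = m in the control arm and μ = m − 1.52 in the fluoxetine arm.
- Mean per arm = p·μ, so the difference is p × 1.52.
- Variance per arm = p·S² + p(1 − p)·μ².
- Common SD = square root of the average of the two variances.

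Example with p = 0.7 and m = 3:
- Difference = 0.7 × 1.52 = 1.064 days.
- Control variance = 0.7 × 3.238 + 0.21 × 9 = 4.16.
- Fluoxetine variance = 0.7 × 3.238 + 0.21 × 1.48² = 2.73.
- SD = √3.44 = 1.855; standardised difference = 1.064 / 1.855 = 0.574.
- Power is 48% at 23 per group and 59% at 30.

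**Step 3: range.** The value m = 1.52 is the most favourable limit, because mean shock time under fluoxetine would then be zero.

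| n per group | p | m = 1.52 | m = 3 | m = 5 |
|---|---|---|---|---|
| 23 | 1.0 | 80% | 80% | 80% |
| 23 | 0.9 | 74% | 69% | 56% |
| 23 | 0.7 | 61% | 48% | 30% |
| 30 | 1.0 | 90% | 90% | 90% |
| 30 | 0.9 | 85% | 80% | 68% |
| 30 | 0.7 | 73% | 59% | 37% |

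At 30 per group, power stays at 80% down to p of about 0.81, 0.90 and 0.95 for m = 1.52, 3 and 5.

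**Step 4: sensitivity to the variance model.** Holding the SD at 1.80 and diluting only the mean gives 71% (p = 0.9) and 50% (p = 0.7) at 23 per group. At 30 per group it gives 82% and 61%, and 80% is kept down to p of about 0.87. The loss does not depend on the widened SD.

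**The case against.** A reader might infer that the effect is certainly diluted and that 80% power is not delivered. The documents do not support that as a fact. They show that shock is not required and that nothing adjusts for it. They give neither p, m nor S, so the size of the loss is conditional throughout. This objection stands.

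The trial also plans 60 patients, not 46. On the plan's own effect and implied SD, 30 per group gives 90% if everyone has shock, and at p = 0.9 two of the three cases above still reach 80%. This stands too. It limits the criticism to the 23-per-group claim and to shock shares below the thresholds shown. The protocol states no expected share that would show the thresholds are met.

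Nor is this a fault of the control arm alone, as comparison with the source's placebo patients might suggest: the case mix is the same in both arms, and the calculation applies p to both.

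The strongest objection is that shock duration is not a named outcome. The outcome list after the Group 2 description makes vasopressor dose primary, with ICU mortality and organ dysfunction secondary. Statistical Analysis and Sample Size makes SOFA primary, at effect size 0.8 and 26 per group. That calculation reproduces (80.7% at 26 per group, 86% at 30) and does not use the shock share. It therefore goes too far to say that a null trial would be misread because shock days were diluted. What remains is that the Sample Size Calculation makes its own sufficiency claim, and the claim is unsupported for the enrolled population. Vasopressor dose is also zero in patients who never need a vasopressor, so the shock share bears on that outcome as well, though no power figure for it can be derived here.

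**Conclusion.** The point holds in a limited form. The effect comes from a septic-shock population, the trial enrols severe sepsis without requiring shock, and no adjustment is made. In every case computed, a shock share below 1 puts 23 per group under 80%. With 10% of patients free of shock the loss is 6 to 24 points; with 30% free of shock it is 19 to 50 points. At 30 per group the target survives only if at least about 81 to 95% have shock, depending on m. All these figures rest on the back-solved SD of 1.80 days and on assumed p and m, so they show how sensitive the claim is and do not estimate the trial's actual power. The calculation does not establish power for either outcome that the protocol calls primary.

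**What to change.** In the Sample Size Calculation:
- Withdraw the statement that 23 per group is sufficient for the enrolled population.
- State the assumed share of patients with shock and the SD, with their basis.
- Reconcile 46, 52 and 60 patients, then restate power over a range of shock shares at the number actually planned.
- Say plainly that shock duration is neither the primary outcome in the outcome list (vasopressor dose) nor the one in Statistical Analysis and Sample Size (SOFA), and that this calculation does not establish power for either.

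Keep the comparison of all randomised patients as the main one. A comparison among patients already on a vasopressor at randomisation may be added as a labelled supportive analysis. If 70% of 30 per group were in that subset, 0.7 × 30 = 21 per group would give 76% on the plan's own effect and implied SD. That figure must be tied to the share on a vasopressor at baseline. It should not be set against the table above, where p is the share who have shock at all, because some patients may start a vasopressor after randomisation.

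The cost is a rewritten section and, if wanted, one supportive analysis, with no extra patients or procedures. The downside is that the stated power becomes less favourable.

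### The 23 per group and 80% power cannot be derived from the stated inputs: no between-patient SD is given, and the claim holds only if the SD of shock duration is no larger than about 1.8 days

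*Protocol*

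**What the plan says.** The protocol's Sample Size Calculation section opens with "The sample size was based on a meta-analysis" and takes from it a "mean reduction in shock duration of $-1.52$ days with corticosteroids compared to placebo", with "95% confidence interval: $-1.71$ to $-1.32". It then states: "Using this effect size, a two-sided alpha of 0.05, and 80% power, we calculated that 23 patients per group (46 total) would be sufficient". It gives no SD and no standardised difference for shock duration, and no other section does.

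Four other places bear on the point:

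- The final Statistical Analysis section names the unpaired t-test for numerical comparisons between the groups.
- Conventional therapy, which both groups receive, includes "IV hydrocortisone at a dose of 200 mg/day" when fluids and vasopressors have not restored stability. Group 2 adds fluoxetine.
- The outcome list after the group descriptions names vasopressor dose as primary. The Statistical Analysis and Sample Size section names SOFA-based organ dysfunction as primary, with a standardised effect of 0.8 and 26 per group.
- Study Population plans 60 patients.

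**The concern.** A mean difference in days becomes a sample size only after it is divided by the between-patient SD. The section calls the raw difference an effect size and moves directly to 23 per group. The only other number it offers is the confidence interval of a pooled mean. That interval narrows as more patients are pooled, so it says nothing about patient-level spread unless the size and weighting of the pool are known.

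The source of the difference adds to the problem. It comes from corticosteroids against placebo, whereas this trial tests fluoxetine on top of care that already includes conditional hydrocortisone. No reason is given why 1.52 days is a suitable target here.

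What is at stake is the 80% power claim. It depends strongly on the one input that is missing, so a reader cannot tell whether a non-significant result on shock duration would be informative.

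**Working it through.** **Inputs from the protocol.** Difference 1.52 days; 95% CI 1.32 to 1.71 in absolute value; two-sided alpha 0.05; power 80%; 23 per group (Sample Size Calculation). Unpaired t-test (Statistical Analysis). 60 patients, taken as 30 per group (Study Population). SD: not given.

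**Step 1. Try to reproduce 23 from what is stated.** The normal-approximation formula is n per group = 2 × (1.96 + 0.842)² × (SD/difference)², which cannot be evaluated without an SD. Two readings that use only the stated numbers were tried:

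- Read 1.52 as a standardised difference: 2 × 2.802² / 1.52² = 6.8, so 7 per group, or 8 by t-test.
- Use the standard error (SE) from the CI as if it were an SD: SE = (1.71 − 1.32)/(2 × 1.96) = 0.0995 days. Then 2 × 2.802² × (0.0995/1.52)² = 0.07, so 1 per group.

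Neither gives 23.

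**Step 2. Solve for the SD that 23 per group requires.**

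- Normal approximation: standardised difference = 2.802 × √(2/23) = 0.826; SD = 1.52/0.826 = 1.84 days.
- t-test (noncentral t, 44 degrees of freedom): standardised difference 0.845; SD = 1.52/0.845 = 1.80 days.

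These are upper limits. Any smaller SD gives more than 80% power.

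**Step 3. Repeat at 30 per group.** The t-test has 80% power for a standardised difference of 0.736, so the largest tolerable SD is 1.52/0.736 = 2.07 days.

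**Step 4. Range for the missing input.** The SDs below are assumptions on both sides of the break-even value. Powers are for 1.52 days, two-sided t-test at 0.05.

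| Assumed SD (days) | Power, 23 per group | Power, 30 per group |
|---|---|---|
| 1.5 | 92% | 97% |
| 1.8 | 80% | 90% |
| 2 | 71% | 82% |
| 2.5 | 52% | 64% |
| 3 | 39% | 49% |
| 4 | 24% | 30% |

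**Step 5. Can the CI supply the SD?** Only with an assumed pooled size N and the simplification that the pool behaves like one equal-arm trial with a common SD. Then SD = SE × √(N/4):

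- N = 100: 0.50 days
- N = 1,000: 1.57 days
- N = 1,300: 1.79 days
- N = 2,000: 2.22 days
- N = 5,000: 3.52 days

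The protocol gives no N, and a meta-analytic SE also depends on study weights and possibly on between-study variance. These values show only that the CI does not determine the SD in either direction.

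**The case against.** The best defence has four parts.

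- **The number may be right.** 23 per group is what a t-test calculation returns for an SD of about 1.76 to 1.80 days, so the authors may have used such a value and left it out. This stands: no miscalculation is shown. It does not rescue the claim, because the SD and its source are not there to be judged.
- **The trial has another basis and a margin.** The calculation of 26 per group for SOFA does reproduce (standardised difference 0.8, t-test, 80% power), and 60 planned patients exceed both 46 and 52. This stands and lowers the severity. However, the SOFA calculation concerns another endpoint, and 30 per group raises the tolerable SD only from 1.80 to 2.07 days.
- **The unfavourable SDs are no better supported than the favourable ones.** This is correct. A reader might infer from the lower rows of the table that the trial is underpowered. The documents do not show that, since they give no reason to prefer an SD of 3 to one of 1.5.
- **The 1.52 days may be only a target difference.** A reader might infer that the protocol expects fluoxetine to act as corticosteroids do. It does not say so. What can fairly be said is that it gives no justification for that target.

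**Conclusion.** The stated 80% power at 23 per group does not follow from the stated inputs. It holds only if the SD of shock duration is no larger than about 1.80 days (1.84 by the normal approximation), or about 2.07 days at 30 per group. Over assumed SDs of 1.5 to 4 days, power runs from 92% to 24% at 23 per group and from 97% to 30% at 30 per group. These figures rest on a t-test with a common SD, equal groups and no loss of patients.

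Two further weaknesses belong to the same section. The target difference is borrowed from a different drug without justification. Shock duration is the primary outcome in neither of the two places where one is declared. The conflict between those two declarations is a separate matter and adds no weight here.

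This is an unsupported power claim, not a proven arithmetic error, and it should be fixed.

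**What to change.** Delete the Sample Size Calculation section as a basis for the trial size, together with its 80% power claim. State one basis, for the single declared primary outcome. For a continuous outcome compared by t-test, it could read: with 30 patients per group and two-sided alpha 0.05, the trial has 80% power to detect a standardised difference of 0.74.

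If a shock-duration calculation is kept, it should:

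- state the between-patient SD and where it comes from;
- recompute the power at the planned number per group;
- justify the target difference for fluoxetine added to the conventional therapy described.

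Do not fill the gap with the back-solved 1.8 days or any other unsourced SD, as that would repeat the fault.

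The cost is wording only, with no change to recruitment or conduct. The drawback is that the stated power may become less favourable once a sourced SD is used.
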